[figure not shown]

## CLINICAL STUDY PROTOCOL

**Title:** The Effects of Low Protein Diet Supplemented with Ketoanalogues on Preservation of Residual Kidney Function among Patients Undergoing Incremental Dialysis

**Key Words:** Residual kidney function, Incremental Hemodialysis, Low Protein Diet, Ketoanalogues

**Rationale:** Residual kidney function may confer a variety of advantages to patients receiving maintenance dialysis including clearance of middle molecule uremic toxins and better volume control. To preserve residual kidney function after initiation of hemodialysis, several strategies should be considered such as minimizing nephrotoxic agents, avoiding of intradialytic hypotension, use of high-flux biocompatible dialyzer, ultrapure water, and online hemodiafiltration (HDF). The recent innovative approaches is a continuation of a low protein diet on non-dialysis day and regular to high protein diet (1-1.2 g/kg/day) on infrequent hemodialysis (HD) days.

In the United States, more than 90% of incident hemodialysis patients initiate a standardized 3-time per week dialysis prescription without intense management to preserve residual kidney function, although there are no convincing evidences that HD prescription based solely required Kt/Vurea provide benefit on patient mortality and quality of life. An alternative approach is “incremental dialysis” aims to provide personalized required HD dose with an intense management to preserve residual kidney function. Meta-analysis revealed that incremental dialysis (once to twice a week) allowed a slower rate of residual kidney function decline (-0.58 ml/min/month,  $p=0.007$ ) compared to a full-dose dialysis and deferred the initiation of thrice weekly HD for approximately 12.1 (95% confidence interval 9.8-14.3) months.

Recent study have suggested a combination of moderately low protein diet (0.6-0.8 g/kg/day) with essential amino acids or ketoanalogues upon this dialysis transition phase. Ketoanalogues reduce burden of uremic toxins given that they lack the amino group bound to the alpha carbon of their respective amino acids and may alleviate the rate of nitrogen waste products removal by the remaining kidney function on non-dialysis interval. In addition, study demonstrated that a diet containing 0.6-0.8 g of protein/kg/day was safe and, when combined with ketoanalogues, was significantly associated with preservation of residual kidney function among peritoneal dialysis patients new to dialysis.

Therefore, we hypothesized that combination of incremental HD and ketoanalogues will better preserve residual kidney function and maintenance of nutritional status among the incident ESRD patients during the early initiation of chronic dialysis. This hypothesis has been a new concept of chronic hemodialysis initiation for ESRD patients

**Purpose:** We plan to conduct the first randomized Phase IIA clinical trial to investigate the efficacy of incremental hemodialysis and moderately low protein diet combined with ketoanalogues

supplementation on preservation of residual kidney function, inflammatory status and nutritional parameters among incident chronic dialysis patients

**Organization:** Division of Nephrology, Faculty of Medicine, Chulalongkorn University, King Chulalongkorn Memorial Hospital

**Objective:**

**Primary objective:** To demonstrate superiority effect of incremental hemodialysis (HD) protocol (initiate with once-weekly HD) plus ketoanalogues-supplemented low-protein diet during non-dialysis days over the standard HD protocol (initiate with twice weekly HD) on preservation of residual renal function (renal urea clearance) at 12 months.

**Secondary objectives**

- To assess whether residual renal function (renal urea clearance) and residual urine volume differ between the two groups over 12 months.
- To determine and compare residual renal function (i.e., renal urea clearance) between the two groups over 12 months.
- To compare nutritional status (serum albumin, muscle mass) between the two treatment groups over 12 months.

**Methods:**

**Sample Size Calculation:**

As this is a pilot study, the sample size calculation will be based on recent suggestions for sample size estimation in pilot randomized trials by Whitehead et al. With 80% power and the alpha level = 5%, 20 patients per treatment arm are required based on the non-central t distribution (NCT) approach assuming a small standardized effect size ( $0.1 \leq \delta < 0.3$ ). With an anticipated the drop-out rate of 20%, 25 patients per treatment arm are adequate. Therefore, we aim to include a total of 50 patients in the study.

Target number of Patients: 50 incident hemodialysis patients will be randomized 1: 1 according to the frequency of dialysis per week, amount of protein prescribed, and receiving of ketoanalogues. Additionally, the different techniques of hemodialysis will be stratified by dialysis facilities as the followings (Fig 1):

- **Group 1:** Twice weekly HD program plus regular protein diet (1.0 g/kg/day) every day
- **Group 2:** Incremental HD program, starting from once weekly HD/HDF plus low protein diet (0.6 g/kg/day) and ketoanalogues supplementation on non-dialysis days and regular protein diet (1.0-1.2 g/kg/day) on dialysis day

[figure not shown]

(Figure S1)

**Both groups receive:**

- Total energy of 30-35 kcal/Kg/day according to age group
- Use BCM method for volume management to avoid intradialytic hypotension and volume overload
- Home BP monitoring for BP control
- Instruction to collect timed urine volume and 24 hours dietary record
- Use of RAAS blockage if appropriate
- Use of loop diuretic if appropriate
- Use of biocompatible high flux dialyzer
- Use of ultrapure water dialysis
- Avoid of nephrotoxic agents and contrast media
- Herbs and other dietary supplement are not allowed
- Nutritional counselling and assessment will be regularly provided by dietitian for patients' education and diet compliance monitoring

**Dialysis protocol during run-in phase before randomization:**

- Low-flux HD for 2 hours \* 1week, (blood flow rate 200 ml/min, dialysate flow rate 400 ml/min) then low-flux HD for 4 hours \* 1week then randomization
- Regular protein diet (1.0 – 1.2 g/kg/day) every day

**Inclusion Criteria:**

- Age ≥ 18 years at screening

- Stable CKD stage 5 not yet on dialysis with residual kidney function 5-10 ml/min/1.73m^2 by CKD-EPI equation
- Urine output  $\geq$  800 ml/day
- Willing to participate in the study and can provide informed consent

**Exclusion Criteria:**

- Rapid glomerular filtration rate (GFR) progression defined as a decline of eGFR  $>5$  ml/min/1.73m^2 by CKD-EPI equation in the prior 6 months before enrollment
- Presence of wasting diseases, cancer cachexia, tuberculosis, AIDS wasting syndrome
- Other active infection/inflammation determined by CRP  $>10$  mg/L
- Severe gastrointestinal problem: persistent nausea/vomiting, dysphagia, chronic diarrhea, severe malabsorption
- Conditions at baseline requiring withdrawal from the study including severe protein energy wasting by SGA and MIS score, prior kidney transplantation with immunosuppressive agents or other serious medical conditions.
- Pregnancy
- Uncontrolled hypercalcemia (persistent serum Ca  $\geq 10.5$  mg/dl)
- BMI  $\geq 35$  kg/m^2
- Hypersensitivity to the active substances or to any of the excipients of Ketosteril
- Disturbed amino acid metabolism

**Criteria for remaining on once-weekly HD for Group 2 (All patients must meet all criteria before randomization)**

- Residual kidney function  $\geq 3$  ml/min/1.73m^2 calculated by Chula urea kinetic model (UKM) formula
- Good dialysis adequacy defined by  $\text{eqKt/V} \geq 1.2$  /session and duration  $\geq 4$  hr/session
- Kru by Chula UKM formula  $< 3$  mL/min
- No signs of water retention (water retention defined as required ultrafiltration rate  $> 15$  ml/kg/hour for 3 consecutive visits)
- No history of active congestive heart failure, ischemic heart disease, acute coronary syndrome, and other pulmonary symptoms
- BMI  $< 35$  kg/m^2
- No persistent hyperkalemia (serum K  $> 5.5$  mEq/L) and hyperphosphatemia (serum phosphate  $> 5.5$  mg/dL) for more than 2 months
- No malnutrition (serum albumin  $< 3.5$  g/dL) and adhere to nutritional therapy
- Hemoglobin  $> 9$  g/dL and appropriate response to anemia therapy
- Infrequent hospitalization and easily manageable other comorbid conditions

**Criteria for remaining on twice-weekly HD for Group 1 and Group 2 (patients should meet first criteria plus  $\geq 5$  of other criteria)**

- Good dialysis adequacy: delivered standard Kt/V  $\geq 2.1$ /week
- No signs of water retention (defined as ultrafiltration rate  $> 15$  ml/kg/hour for 3 consecutive visits)
- No history of active congestive heart failure, ischemic heart disease, acute coronary syndrome, and other pulmonary symptoms

- Suitable larger body size relative to RKF
- No persistent hyperkalemia (serum K >5.5 mEq/L) and hyperphosphatemia (serum phosphate >5.5 mg/dL) for > 1 months or 2 consecutive visits (2-week interval)
- No malnutrition (serum albumin <3.5 g/dL) and adhere to nutritional therapy
- Hemoglobin >8 g/dL and appropriate response to anemia therapy (erythropoietin dose adjustment is allowed for 1 visit)
- Infrequent hospitalization and easily manageable other comorbid conditions

After the protocol approval by IRB of Faculty of Medicine, Chulalongkorn University, the participants that willing to participate the study will sign in the informed consent. They will get into run-in period and then randomization.

After randomization, the attending nephrologists at each time point (3, 6, 9, and 12 months after randomization) will determine HD frequency by criteria. The HD frequency will be increase from once per week to twice per week in Group 1, if patients fail criteria for remaining on once per week HD. The HD frequency will be increase from twice per week to thrice per week in Group 2, if patients fail criteria for remaining on twice per week HD. Patients in Group 1 receiving twice per week HD will receive thrice per week HD if patients fail criteria for remaining on twice per week HD.

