#### Chula UKM formula:

$$C = C_0 \cdot e^{-k \cdot t} = C_0 \cdot e^{-\frac{K_d \cdot t}{V}}$$

$$\frac{K_d \cdot t}{V} = \ln\left(\frac{C_0}{C}\right)$$

- In is the natural logarithm;
- C0 is urea concentration at the start of dialysis
- K is dialyzer clearance
- T is dialysis time
- V is volume distribution of urea

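### The once-weekly HD criteria set two opposed residual-function cut-offs (RKF at least 3, Kru below 3), and the equation printed as their source has no renal term

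*Protocol*

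**What the plan says.** The list headed Criteria for remaining on once-weekly HD for Group 2 stands in the Protocol under Exclusion Criteria and has ten items. Its heading adds "All patients must meet all criteria before randomization", so the list is an entry condition for both arms as well as a rule for staying on once-weekly treatment.

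- Item 1: residual kidney function (RKF) of at least 3 ml/min/1.73m2, "calculated by Chula urea kinetic model (UKM) formula".
- Item 3: "Kru by Chula UKM formula", which must be below 3 mL/min.

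The Addendum prints one equation under the name Chula UKM formula: Kd·t/V = ln(C0/C). Its key states "K is dialyzer clearance"; the other terms are urea concentrations, dialysis time and urea distribution volume.

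The text after the criteria has the attending nephrologists decide HD frequency by these criteria at 3, 6, 9 and 12 months. The Measurement table separately schedules urinary urea clearance from timed urine at baseline and at those same four visits.

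The Protocol does not hold to one meaning of residual function. The Inclusion Criteria admit patients "not yet on dialysis with residual kidney function 5-10" by the CKD-EPI equation, which is an eGFR. The primary objective is "preservation of residual renal function (renal urea clearance) at 12 months", which is a urea clearance.

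**The concern.** A list meant to pick out patients with enough kidney function for one session a week should set a floor on that function. Item 1 does so. Item 3 sets a ceiling at the same number, so better function counts as failure. Both items are mandatory, so the ceiling cannot be outvoted by the rest of the list.

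Two decisions depend on it. The first is entry: followed literally, a patient with Kru of 3 mL/min or more may not be randomized. The second is the step from once to twice a week, where a patient would be moved up because residual function is good. HD frequency is a main component of the randomized intervention, so a misdirected step-up rule changes the treatment being tested.

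The source given for both values adds a second difficulty. A nephrologist who turns to the Addendum finds an equation that returns neither of them.

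**Working it through.** **1. Item 3 alone.** The requirement is Kru < 3 mL/min, so Kru ≥ 3 mL/min fails. This needs no assumption about RKF or body size.

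**2. Items 1 and 3 together.** The Protocol does not say how RKF and Kru relate. Assume both are renal urea clearance and that item 1 is only indexed to body surface:

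RKF = Kru × 1.73/BSA

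Item 1 then requires Kru ≥ 3 × BSA/1.73, and item 3 requires Kru < 3. The pair needs

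3 × BSA/1.73 ≤ Kru < 3

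The Protocol gives no BSA distribution, so the result is shown over a range:

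| BSA (m2) | Lower bound for Kru (mL/min) | Upper bound | Width |
|---|---|---|---|
| 1.4 | 3 × 1.4/1.73 = 2.428 | 3.000 | 0.572 |
| 1.5 | 3 × 1.5/1.73 = 2.601 | 3.000 | 0.399 |
| 1.6 | 3 × 1.6/1.73 = 2.775 | 3.000 | 0.225 |
| 1.7 | 3 × 1.7/1.73 = 2.948 | 3.000 | 0.052 |
| 1.73 | 3.000 | 3.000 (excluded) | none |
| 1.8 | 3 × 1.8/1.73 = 3.121 | 3.000 | none |

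On this reading the window is narrow for smaller patients and closes at 1.73 m2.

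**3. The printed equation.** The terms in Kd·t/V = ln(C0/C) are set beside what the two items need:

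- Present: starting urea concentration C0, later urea concentration C, dialyzer clearance Kd, session time t, urea volume V.
- Absent: Kru, urinary urea, urine volume, interdialytic interval.

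The output is dialyzer Kt/V for one session, and there is no renal unknown to solve for.

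A numerical check uses assumed values that are not in the Protocol: Kd 200 mL/min, t 240 min, V 35,000 mL. The printed equation gives 200 × 240/35,000 = 1.371. Adding a true renal clearance to the decay during the session gives ln(C0/C) = (200 + Kru) × 240/35,000:

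- Kru 0: 1.371
- Kru 3: 1.392
- Kru 6: 1.413

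The whole range from 0 to 6 mL/min moves the result by about 0.04. An error of 5% either way in Kd moves it from 1.303 to 1.440, about 0.14. So even an attempt to infer Kru from the fall in urea during a session would be swamped by ordinary uncertainty in Kd.

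**The case against.** The best defence concerns the equation. The Addendum is short, its key does not define C, and it uses k, K and Kd loosely. It may print only the basic decay step of a fuller institutional model that does return Kru. This stands. The documents show that the printed equation is insufficient; they do not show that the model used at the institution is. A reader might also infer that clinicians will have to improvise and will reach different decisions. Nothing in the Protocol shows that staff lack the model or would diverge, and the timed-urine urea clearance is an obvious value for Kru at each decision visit.

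On the cut-offs, a reader might infer that no patient can qualify. The documents do not support that: even under BSA indexing a window remains below 1.73 m2, and the indexing is itself an assumption. One could instead take RKF as the mean of urinary urea and creatinine clearance, also in the Measurement table, and then the two items can coexist more easily. But item 1 names a urea kinetic model, which does not yield creatinine clearance, so that reading fits the text poorly. On any reading, item 3 still fails a patient for having Kru of 3 mL/min or more.

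It is also fair to say that the entry condition applies alike to both arms, that these are two of ten items, and that this is a 50-patient pilot with P values treated as exploratory. Those points limit the consequence. They do not make the rule right as written.

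**Conclusion.** The point holds, and the opposed cut-offs are the main defect. That item 3 fails patients with Kru of 3 mL/min or more follows from the text alone, taking Kru in its usual sense of renal urea clearance. The window of 2.77 to 3.00 mL/min at 1.6 m2, and its closing at 1.73 m2, depend on the unstated BSA indexing. The insufficient equation is a secondary defect: two of ten criteria cite a source that, as printed, cannot supply them.

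How many patients would be affected cannot be derived, because the Protocol gives neither a Kru nor a BSA distribution and defines entry-level function by eGFR.

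A reader might infer that the primary result is compromised. The documents do not support that for its measurement, since renal urea clearance comes from timed urine and does not use the printed equation. The effect is confined to who enters and when HD frequency is raised. It should be corrected, but it does not undermine the design.

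One related slip is a separate matter. The step-up rule is written as "from once per week to twice per week in Group 1, if patients fail criteria for remaining on once per week HD", although Group 2 is the arm on the "Incremental HD program, starting from once weekly HD/HDF plus low protein diet". I read the rule as meaning Group 2.

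**What to change.** In the once-weekly criteria:

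1. Keep one consistent residual-function criterion by correcting or deleting whichever of the two cut-offs was not intended. The investigators should confirm its direction and value.
2. Define it as the timed-urine urea clearance in the Measurement table, and state whether it is in mL/min or per 1.73 m2.
3. Either remove the attribution to the Addendum equation, or replace that equation with the full model, including its Kru term and a complete key.

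The cost is a text change in the criteria and the Addendum. No new measurement is needed, because the timed-urine urea clearance is already scheduled at baseline and at each visit where HD frequency is decided. The correction does not require moving the baseline collection: the Protocol places it at randomization and does not say that its result comes afterwards.

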#### Adverse events, serious adverse events,

Adverse events leading to premature discontinuation and all events resulting in death will be assessed throughout the study.

**Investigation period:** 12 months 2 weeks (run-in: 2 weeks + evaluation 12 months)

**Data collection:** 5 points (Baseline at randomization, 3, 6, 9, and 12 months after randomization)

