#### Measurement:

[figure not shown]

Primary outcomes

[figure not shown]

Secondary outcomes

|  | Baseline | 3 months | 6 months | 9 months | 12 months |
|--|----------|----------|----------|----------|-----------|
|  |          |          |          |          |           |

|                                                                                                                      |   |       |   |       |   |
|----------------------------------------------------------------------------------------------------------------------|---|-------|---|-------|---|
| Urinary urea clearance by timed-urine volume (24 hours preceding dialysis treatment)                                 | X | X     | X | X     | X |
| Average of urinary urea and creatinine clearance (24 hours preceding dialysis treatment)                             | X | X     | X | X     | X |
| Nutritional parameters: weight, BMI, albumin, calcium, phosphate level, normalize protein catabolic rate (nPCR), SGA | X | X     | X | X     | X |
| Bioimpedance analysis                                                                                                | X | X     | X | X     | X |
| Other functional tests QoL (SF 36), B2microglobulin, P-cresol, indoxyl sulfate, anemia                               | X | ----- | X | ----- | X |

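### The formula named for residual kidney function and Kru in the once-weekly criteria has no renal term, and the two limits it is meant to supply conflict

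*Protocol*

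**What the plan says.** Protocol, Criteria for remaining on once-weekly HD for Group 2. The heading adds that "All patients must meet all criteria before randomization", so the list is an entry condition as well as a rule for staying on once-weekly HD. Two of its lines concern residual function:

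- residual kidney function of at least 3 ml/min/1.73m², "calculated by Chula urea kinetic model (UKM) formula";
- "Kru by Chula UKM formula" below 3 mL/min.

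Protocol, Addendum, Chula UKM formula. The equation is C = C0·exp(−Kd·t/V), rearranged to Kd·t/V = ln(C0/C). The legend says "K is dialyzer clearance"; the time is time on dialysis and V is the urea distribution volume.

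Protocol, Measurement. The schedule has a row for "Urinary urea clearance by timed-urine volume (24 hours preceding dialysis treatment"), marked at every visit, and a second row for the average of urea and creatinine clearance. Data collection is at five points: "Baseline at randomization, 3, 6, 9, and 12 months after randomization". Nothing links these rows to the frequency criteria.

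Protocol, Criteria for remaining on twice-weekly HD. The list opens with "Good dialysis adequacy: delivered standard Kt/V" of at least 2.1/week, citing a haemodialysis adequacy guideline. This item is compulsory: "patients should meet first criteria plus" at least five others. The text does not say whether renal clearance counts.

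**The concern.** The protocol names a method and prints it, and the printed method cannot give the quantity it is named for. Because the method is printed, this is not detail left to a statistical analysis plan.

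The affected lines decide who may be randomized and when a patient leaves once-weekly HD at the 3-, 6-, 9- and 12-month reviews. Dialysis frequency is part of the randomized contrast, and loss of renal urea clearance over 12 months is the primary endpoint. If each nephrologist substitutes a private method for the unusable formula, eligibility and delivered frequency will vary in ways that the protocol does not control.

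The two lines also point in opposite directions: one asks for residual function of 3 or more, the other for less than 3. The silence on renal clearance in the 2.1/week item is a lesser problem of the same kind.

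**Working it through.** The protocol derives no figure here, so there is none to reproduce.

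**1. What the printed formula can return**

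Its terms are dialyzer clearance, dialysis time, urea volume, and urea concentration at the start (C0) and later in the session (C). It has no renal clearance, urine urea, urine volume, urea generation or interdialytic interval. The only output is Kd·t/V for one session. Reading K as dialyzer plus renal clearance does not help, because one equation cannot separate the two. The renal share would also be tiny: for Kru 3 mL/min over 240 min with V assumed at 33 L, 3 × 240 / 33,000 = 0.022, against about 1.2 in total.

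**2. Whether the two limits can hold together**

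Take both lines as urea clearance from one collection, which is an assumption. With body surface area BSA, the first line requires Kru × 1.73/BSA ≥ 3, so Kru ≥ 3 × BSA/1.73. The second requires Kru < 3.

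- BSA = 1.73 m²: Kru ≥ 3 and Kru < 3, which is impossible. It is also impossible at any larger BSA.
- BSA = 1.6 m² (assumed): 3 × 1.6/1.73 = 2.77, so only 2.77 ≤ Kru < 3.0 passes.

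Moving both lines to the same urine result would therefore leave almost nobody eligible. The conflict has to be resolved in the same edit.

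**3. The 2.1/week item by dialysis alone**

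Inputs: N = 2 sessions per week and t = 240 min. The 4 h and eqKt/V 1.2 come from the once-weekly list; the twice-weekly list gives neither, so using them there is an assumption. The protocol prints no equation for standard Kt/V. The usual fixed-volume, steady-state form is used, with x the eqKt/V per session:

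stdKt/V = [10080(1 − e^−x)/t] / [(1 − e^−x)/x + 10080/(N·t) − 1]

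At x = 1.2: 29.35/20.58 = 1.426.

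| eqKt/V per session | 1.2 | 1.4 | 1.6 | 1.8 | unlimited |
|---|---|---|---|---|---|
| standard Kt/V per week | 1.43 | 1.54 | 1.64 | 1.71 | 42/20 = 2.10 |

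The ceiling is 2.07 for 3 h and 2.13 for 5 h. A single-pool simulation with 3- and 4-day gaps gives the same 1.426 at x = 1.2. With an assumed 2 L gain between sessions and V 33 L, the result is about 1.5 to 1.8 at eqKt/V 1.2 to 1.8, and 2.1 is reached at about 3.3 per session.

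**4. The same item with renal clearance counted (illustration; V assumed, eqKt/V 1.2)**

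Simple addition requires Kru = (2.10 − 1.426) × V/10.08, with V in litres. Solving Kru inside the kinetic model gives higher values:

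| V (L) | 25 | 33 | 40 |
|---|---|---|---|
| Kru needed, added (mL/min) | 1.67 | 2.21 | 2.67 |
| Kru needed, in the model (mL/min) | 2.43 | 3.21 | 3.89 |

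The rule then works, but the Kru at which a patient steps up moves by 0.8 to 1.2 mL/min with the method.

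**The case against.** The strongest reply concerns the 2.1/week item. It cites a guideline that may define how renal clearance is credited, and that source is not at hand. The trial is about residual function, and another item on the same list relates body size to it, so counting renal clearance is the likely intent. The standard Kt/V equation, V, fluid gain and twice-weekly session dose all come from outside that item. This objection stands and keeps this part to a clarification.

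A reader might infer from the 2.10 ceiling that every twice-weekly patient must step up, or that nobody could pass. The figures do not support that. The ceiling is 2.13 for 5 h sessions, and with fluid gain 2.1 is reached at about 3.3 per session. What holds is narrower: 2.1 is out of reach at usual doses, and only if renal clearance is left out.

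A reader might also infer that the primary endpoint is miscalculated. It is not. The schedule measures urinary urea clearance from timed urine at all five points, and the printed formula does not enter it. Any effect on the endpoint runs through eligibility and dialysis frequency, and its size is not known. The same collection gives clinicians a usable Kru in practice, but the criteria name a different source.

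None of this answers the mismatch between the once-weekly criteria and the Addendum, or the opposing limits.

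**Conclusion.** The point holds for the once-weekly criteria and should be fixed. Residual kidney function and Kru are required from a formula that yields only session dialyzer Kt/V, so neither line can be evaluated as written. This follows from the printed terms and needs no outside input.

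The opposing limits make the problem worse. If both are urea clearance, they cannot be met together at BSA of 1.73 m² or more, and they leave a band of about 0.2 mL/min at an assumed 1.6 m². If they were meant as two different quantities, the protocol does not say which.

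The 2.1/week item is a minor, secondary clarification. Dialysis alone gives about 1.4 to 1.8 per week for two 4-hour sessions at eqKt/V 1.2 to 1.8, under the assumptions listed. Nothing in the protocol shows that renal clearance is meant to be excluded. This is a correction to the text, not a fatal flaw in the design.

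**What to change.** 1. **Addendum.** Confine the printed formula to session dialyzer Kt/V, or print the version that contains Kru.
2. **Once-weekly list.** Take residual function from the timed 24-hour urine collection in the Measurement schedule, and require the baseline result to be read before randomization.
3. **Conflicting pair, in the same edit.** Keep one residual-function criterion in one direction (at least 3) and delete or reverse the Kru line. Alternatively, assign the two lines to different named quantities in the schedule (urea clearance, and the average of urea and creatinine clearance) with compatible cut-offs.
4. **Twice-weekly list.** State that 2.1/week is total standard Kt/V, dialysis plus renal, by one named calculation, including the method for V, used in both arms. Which calculation is chosen matters less than stating it.

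The cost is a few lines of text. No new measurement is needed, because urine is already collected at all five points; the only operational change is having the baseline result in hand before randomization.

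### The once-weekly HD list requires residual kidney function of at least 3 and also Kru below 3, so any patient with Kru of 3 mL/min or more fails it, at entry and at later reviews

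*Protocol*

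**What the plan says.** The list of criteria for remaining on once-weekly HD (Protocol, under Exclusion Criteria) opens with the rule "All patients must meet all criteria before randomization". Two of its bullets concern residual function:

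- The first sets a floor of 3 ml/min/1.73m², "calculated by Chula urea kinetic model (UKM) formula".
- The third sets a ceiling: "Kru by Chula UKM formula" must be below 3 mL/min.

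The same list is used after randomization. At months 3, 6, 9 and 12 the attending nephrologists "will determine HD frequency by criteria", and the consequence of failing is stated as: "The HD frequency will be increase from once per week to twice per week in Group 1, if patients fail criteria". The reference to Group 1 appears to be a slip. Only Group 2 begins on once-weekly treatment (Sample Size Calculation: "starting from once weekly HD/HDF plus low protein diet"), so the step is read here as applying to Group 2.

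The primary objective is "preservation of residual renal function (renal urea clearance) at 12 months", which treats residual renal function and renal urea clearance as the same thing.

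**The concern.** A floor and a ceiling with the same number, derived from the same named formula, both have to be met. The ceiling excludes exactly the patients whose function is better preserved.

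Two decisions depend on this list. The first is who may be randomized. The second is dialysis frequency in Group 2, which is part of the randomized intervention. Applied as printed, the list turns away candidates with higher Kru. At a review it also increases dialysis for a Group 2 patient whose Kru has held at, or recovered to, 3 mL/min or more. Dose would then be escalated on the endpoint variable in the wrong direction. If nephrologists each repair the rule in their own way, eligibility and dose will differ between them for reasons the protocol does not record.

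**Working it through.** **Step 1: the logic, with no assumption.** All bullets must hold and one of them is Kru < 3 mL/min. Kru values of 3, 3.5, 4 and 5 mL/min all fail it, whatever the first bullet measures.

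**Step 2: can the bullet be read as a failing value?** The water-retention, potassium/phosphate and malnutrition bullets give a failing value, but each opens with a negation. The Kru bullet has none. It has the same form as the BMI and hemoglobin bullets, which are plain requirements.

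**Step 3: do the different units rescue it?** The floor is indexed to 1.73 m² and the ceiling is not. Assume both describe one clearance, with indexed value = Kru × 1.73/BSA. The protocol gives no BSA values, so a range is assumed. Both bullets hold only if 3 × BSA/1.73 ≤ Kru < 3.

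| BSA (m²) | Lowest Kru meeting the floor (mL/min) | Kru range meeting both | Ceiling on the indexed scale, 3 × 1.73/BSA |
|---|---|---|---|
| 1.4 | 2.43 | 2.43 to <3 | 3.71 |
| 1.5 | 2.60 | 2.60 to <3 | 3.46 |
| 1.6 | 2.77 | 2.77 to <3 | 3.24 |
| 1.7 | 2.95 | 2.95 to <3 | 3.05 |
| 1.73 | 3.00 | none | 3.00 |
| 1.8 | 3.12 | none | below the floor |

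**Step 4: a more generous reading of the floor.** The Measurement table also schedules the average of urinary urea and creatinine clearance. Suppose the first bullet meant that average, with creatinine clearance equal to r × Kru (r assumed 1.25 to 2.0). The floor becomes Kru ≥ (3 × BSA/1.73) × 2/(1 + r). At BSA 1.6 this is 2.47 (r = 1.25), 2.22 (r = 1.5) or 1.85 (r = 2.0). No value satisfies both bullets from BSA = 1.73 × (1 + r)/2, which is 1.95, 2.16 or about 2.6 m². The band widens, but the ceiling at Kru < 3 does not move.

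**Step 5: how many patients? (illustration only).** The entry range of 5–10 ml/min/1.73m² is a CKD-EPI estimate, a different measure from Kru, so it does not supply a Kru distribution. A simulation therefore assumed normal indexed Kru (mean 3 to 6, SD 0.5 to 1.5) and normal BSA (mean 1.4 to 1.7, SD 0.15), with 1,000,000 draws per setting.

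- The share meeting both bullets ran from under 0.1% (mean 6, SD 0.5, BSA mean 1.6 or 1.7) to about 48% (mean 3.5, SD 0.5, BSA mean 1.4).
- With mean 3.5 and SD 1.0 it was 28.2%, 19.1%, 11.3% and 5.7% at BSA means 1.4, 1.5, 1.6 and 1.7.

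**Step 6: later reviews (illustration only).** Take patients who met both bullets at entry, drawn from mean 4, SD 1.0, and apply a three-month change with SD 0.5 on the indexed scale.

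- Mean change −0.3: 36% to 55% then fall below the floor and 10% to 17% fail the ceiling, across BSA means 1.4 to 1.7.
- No mean change: 23% to 35% fail the ceiling.

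Only the ceiling failures measure the defect. Failing the floor is the rule doing what it was meant to do.

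**The case against.** The strongest reply is that this is an obvious drafting slip. A nephrologist who sees the floor of 3 two lines above would ignore or reverse the ceiling, just as the Group 1 slip is read here by its sense. That may happen. But the text does not say which repair is right (a reversed sign, a stray trigger or another threshold), so common sense does not guarantee one rule across clinicians.

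The effect at later reviews is partly inference, and this point stands. The requirement to meet every criterion is printed with reference to the time before randomization, and no count is given for the once-weekly list at review. The twice-weekly list does give one: its first criterion plus at least five others. Still, the list is titled as criteria for remaining on once-weekly HD, the step-up follows from failing those criteria, and the only rule printed for them is that all must be met.

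Strict use as an entry gate can also be doubted. Some bullets refer to abnormalities lasting more than two months, while the run-in lasts two weeks. That shows the list fits its entry role poorly, but it does not cancel the printed requirement.

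The simulation is fairly criticised. Its inputs are chosen, and the share meeting both bullets also counts patients who fail the legitimate floor. Applying the assumed decline to unindexed Kru instead gives 44% to 58% floor failure. The averaged-clearance reading has little support in the wording of the first bullet. Neither is needed for the conclusion.

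Finally, the Chula UKM formula printed in the Addendum contains dialyzer clearance only, with no residual-kidney term. That is a separate defect. It needs its own correction, and deleting a bullet does not touch it.

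**Conclusion.** The concern holds. As printed, Kru of 3 mL/min or more fails the once-weekly list. This needs no assumption for entry; for later reviews it needs only the natural reading that the same list applies in full and that Group 2 is meant. If both bullets describe the same clearance with BSA indexing, the band that meets both is at most 0.57 mL/min wide over the BSA values considered (3.00 − 2.43 at 1.4 m²) and is empty from 1.73 m² upward.

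The share of patients affected is unknown. The simulated range of under 0.1% to about 48% meeting both bullets shows only that it could be large. It is not claimed that nobody can enter, or that the difference in HD frequency between the arms disappears. Because the contradiction sits in a rule governing both eligibility and the randomized dialysis dose, and works against the trial's aim, it must be corrected.

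**What to change.** Delete the bullet setting Kru below 3 mL/min. Alternatively, take it out of the list and restate it as the trigger for moving from once- to twice-weekly HD. Keep a single residual-function floor of at least 3, in one stated unit (indexed or unindexed), for both entry and remaining on once-weekly HD, and have the investigators confirm that threshold. State in the same amendment that the full list applies at each review and that the once-to-twice step concerns Group 2.

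The core change is one line and calls for no new measurement. The remaining cost is a check of patients already screened out or stepped up under the printed list.
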